**Fig 1 pone.0358221.g001:**
[figure not shown]
SPIRIT schedule of enrollment, interventions, and assessments. ERV, energy recovery ventilator; PAC, portable air cleaner; ACT, asthma control test; C-ACT, childhood asthma control test; ACQ, asthma control questionnaire; SF-36, 36-item short form health survey; PedsQL, pediatric quality of life inventory; PSS, perceived stress scale; PSS-C, perceived stress scale–child; PROMIS, patient-reported outcomes measurement information system.

### Participant recruitment

The target study population includes children aged 5–17 years and adults aged 18 years and older with asthma from 80 households. Initially, approximately 88 households will be recruited to account for potential dropout and ensure that the required sample size is maintained throughout the study period. Participants will be primarily recruited from applicants to Rebuilding Together North Texas (RTNTX), a nonprofit organization that administers the Safe & Healthy Homes program. This program provides essential home repairs, safety improvements, and accessibility modifications for low-income residents across diverse communities in the DFW area.

Eligibility requirements for participation in the study include: (1) homes must have at least one occupant with self-reported physician-diagnosed asthma; (2) homes must be non-smoking; (3) homes must be owner-occupied; and (4) participants must agree to participate in the entire 2-year study duration and allow for five home visits by the research team. Potentially eligible participants will complete an electronic screening form prior to enrollment, based on the inclusion and exclusion criteria listed below.

The inclusion criteria:

Age: children 5–17 years; adults ≥18 years.Individuals with physician-diagnosed asthma.Residency in the DFW area.English speaking and writing.Able to provide consent.Able to communicate regularly by phone.

The exclusion criteria:

Homes with any current smokersAnticipated relocation outside the DFW area within the two-year study period.Hazardous conditions and/or safety concerns in or around the participant’s home.Use of any device not provided as part of the study, including ERVs or portable HEPA air cleaners, in the participant’s home at any time during the trial.

Participant engagement will be maintained through home visits and monthly asthma surveys via phone. Primary participants will receive a total of $200 in gift cards across the four follow-up visits (V1-V4), and additional eligible family members may receive $100 each. Participants will have the option to keep the intervention device; those assigned to a sham device will receive an active device at study completion. Participants who do not complete required assessments will not be randomized or remain in the study. Compensation is contingent upon completing all study procedures, and participants who withdraw or fail to complete visits will forfeit subsequent payments.

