For the 40 homes assigned to the ERV intervention, we will install a Broan-NuTone B160E75RS/T units. The required airflow rate of each unit will be determined based on the floor area and number of bedrooms, in accordance with ASHRAE Standard 62.2–2025, *Ventilation and Acceptable Indoor Air Quality in Residential Buildings* [36]. The building envelope leakage measured during the initial home assessments will be applied as infiltration credits in the ventilation rate calculations to account for natural air leakage. The ERV units will then operate continuously at the specified ventilation rate throughout the intervention period.

Sham ERVs will be installed in the same manner as active units but will be programmed to operate in recirculation mode, without supplying outdoor air or altering ventilation rates. They will draw indoor air from the home and return it without any dilution or exchange with outdoor air, as the outdoor air intake damper remains closed. Participants will not have access to the control panel settings during the study period. This modification will maintain participant blinding, as occupants will experience airflows and fan noise similar to those of active ERVs.

Forty (40) homes in the air cleaner group will receive a Medify Air MA-112 unit, primarily placed in the living room (or in the bedroom if occupants spend the majority of their time). In cases where additional eligible family members reside in the same household, an additional Medify Air MA-50 unit will be deployed in their bedrooms. Both air cleaners are equipped with HEPA and activated carbon filters. In homes assigned to the sham control group, filters will be removed from the air cleaner units. Both active and sham air cleaner units will be sealed and have identical external appearance and installation configurations to maintain participant blinding.

During scheduled home visits in the post-intervention period, field staff will check the ERV and air cleaner units to verify proper operation and confirm that blinding measures are maintained, including ensuring that ERV control panel settings remain unchanged and inaccessible to participants and that air cleaner unit seals remain intact.

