### Power calculations

The sample size and statistical power for this 4-arm parallel-group randomized controlled trial is analyzed for various scenarios based on a range of likely magnitudes of outcomes for asthma-related health outcome and environmental exposure assessments (Table 1). Calculations are made utilizing a robust statistical software tool, G*Power ver. 3.1.9.7, for a repeated measures ANOVA with a within-between interaction [49]. A range of effect sizes from small (Cohen’s f = 0.10), medium (f = 0.25), to large (f = 0.40) are considered to accommodate varying expected intervention effects, ensuring both robustness and generalizability of the findings [50]. Sample size calculations were conducted for the health outcomes (ACT and PFT) and environmental outcomes (IAQ and mold measurements). Required sample sizes were estimated based on expected effect sizes to achieve a statistical power >0.80 and adjusted for a 10% dropout rate. For monthly ACT surveys (n = 24) and monthly average low-cost IAQ measurements (n = 24), the required sample sizes ranged from 84 households for a small effect size (0.10) to 9 households for a large effect size (0.40). For PFT and mold measurements, the required sample sizes were estimated at 220 and 308 households, respectively, for detecting a small effect size (0.10); 40 and 53 households, respectively, for a medium effect size (0.25); and 18 and 26 households, respectively, for a large effect size (0.40). Although larger sample sizes were required to detect a small effect size (0.1) for PFT and mold, these estimates represent the sample sizes needed to detect very small changes. Further, the AIRVAC study was primarily designed to evaluate intervention effects on asthma outcomes and IAQ, for which the estimated sample sizes were within the planned recruitment range. Therefore, the final target sample size was set at 80 households, with an initial recruitment target of 88 households to account for potential dropout.

**Table 1 pone.0358221.t001:** Sample size calculations.

Effect Size (Cohen’s f for ANOVA)	Small			Medium			Large
	0.1	0.15	0.2	0.25	0.3	0.35	0.4

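### The 10% dropout adjustment multiplies by 1.10 instead of dividing by 0.90, and the 40 + 40 homes described for devices are not reconciled with the 88 to be recruited

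*Protocol article*

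**What the plan says.** Participant recruitment sets the target: "The target study population includes children aged 5–17 years and adults aged 18 years and older with asthma from 80 households". It then says that "approximately 88 households will be recruited to account for potential dropout and ensure that the required sample size is maintained throughout the study period". Power calculations repeats this: "the final target sample size was set at 80 households, with an initial recruitment target of 88 households to account for potential dropout". The required sizes there were estimated "to achieve a statistical power >0.80 and adjusted for a 10% dropout rate", and Table 1 has a row of totals so adjusted for each outcome and effect size. For the monthly ACT and IAQ measurements at f = 0.10, Table 1 gives 76 before and 84 after the adjustment.

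Randomisation follows a pre-intervention period of up to one year, and a one-year post-intervention period follows it (Study design, Interventions). Losses are foreseen in both: "Participants who do not complete required assessments will not be randomized", and the same sentence adds that such participants do not remain in the study.

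The device description in Interventions counts 80 homes: "For the 40 homes assigned to the ERV intervention" and "Forty (40) homes in the air cleaner group will receive a Medify Air MA-112 unit". Environmental exposure assessments plans 160 low-cost sensors, placed indoors and outdoors from V1. The abstract speaks of more than 80 households.

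**The concern.** An allowance for a 10% loss has to be computed on the number recruited, because that is the number from which the loss is taken. Adding 10% to the number needed gives too few. The adjusted row of Table 1 therefore does not do what its label says, and 88 does not quite keep 80.

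The second matter is where the reserve sits. The article promises that the size is kept through the whole study, but its device figures add up to 80, not 88, at a point when up to a year of losses has already occurred and another year lies ahead. If those figures are the number randomised, the reserve can only replace homes lost before randomisation, and a full complement of more than 80 homes would leave some without a described device. At stake are the correctness of the published sample-size figures and a clear statement of how many homes enter the randomised comparison.

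**Working it through.** **Inputs.** Target 80, recruitment about 88, dropout 10%, and the Table 1 totals (Power calculations). Devices for 40 + 40 homes (Interventions). Alpha 0.05 and four groups (Table 1 footnote, Study design). The article does not state the correlation among repeated measures or the sphericity correction. I assume correlation 0.5 and epsilon 1.

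**Reproducing the plan's figures.**
- 80 × 1.10 = 88, the stated recruitment target.
- All 21 adjusted totals equal the unadjusted total × 1.10, rounded to the nearest whole number (for example 76 × 1.10 = 83.6, shown as 84).
- Power for the within-between interaction uses a noncentral F with λ = f² × N × m / (1 − ρ) and degrees of freedom (k − 1)(m − 1) and (N − k)(m − 1). With N = 76, m = 24, k = 4, f = 0.10: λ = 0.01 × 76 × 24 / 0.5 = 36.48, degrees of freedom 69 and 1656, power 0.815. Table 1 states 0.82.
- On these assumptions 20 of the 21 power entries reproduce within two percentage points. The exception (f = 0.40, 24 measurements, N = 8: 0.898 against 0.92) has no bearing here.

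**Check of the dropout adjustment.** After a loss d, the number left is recruited × (1 − d), so the number to recruit is N / (1 − d).
- 88 × 0.90 = 79.2. Keeping 80 needs 80 / 0.90 = 88.9, so 89.
- Each adjusted total × 0.90, set against its own requirement:

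| Measurements | Effect size f | Required | Adjusted in Table 1 | Left after 10% loss | N/0.90, rounded up |
|---|---|---|---|---|---|
| 24 (ACT, IAQ) | 0.10 | 76 | 84 | 75.6 | 85 |
| 24 | 0.20 | 24 | 26 | 23.4 | 27 |
| 24 | 0.30 | 12 | 13 | 11.7 | 14 |
| 24 | 0.35 | 12 | 13 | 11.7 | 14 |
| 4 (PFT) | 0.10 | 200 | 220 | 198.0 | 223 |
| 4 | 0.15 | 92 | 101 | 90.9 | 103 |
| 4 | 0.20 | 52 | 57 | 51.3 | 58 |
| 4 | 0.30 | 28 | 31 | 27.9 | 32 |
| 4 | 0.35 | 20 | 22 | 19.8 | 23 |
| 2 (mold) | 0.10 | 280 | 308 | 277.2 | 312 |
| 2 | 0.15 | 128 | 141 | 126.9 | 143 |
| 2 | 0.20 | 76 | 84 | 75.6 | 85 |
| 2 | 0.25 | 48 | 53 | 47.7 | 54 |
| 2 | 0.35 | 28 | 31 | 27.9 | 32 |
| 2 | 0.40 | 24 | 26 | 23.4 | 27 |

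These are the 15 totals that fall short. Eleven do so by less than one household, and four by 1.1 to 2.8 (required 200, 92, 280 and 128). The other six totals are right as printed.

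**Check of the number randomised.** 40 + 40 = 80. If 80 are randomised, the homes left at the end of the post-intervention year are 80 × 0.95 = 76 after a 5% loss and 80 × 0.90 = 72 after a 10% loss. Power at f = 0.10 with 24 measurements:

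| Homes | 88 | 80 | 79 | 76 | 75 | 74 | 72 |
|---|---|---|---|---|---|---|---|
| Power | 0.890 | 0.844 | 0.837 | 0.815 | 0.808 | 0.7998 | 0.783 |

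The threshold of 0.80 is therefore reached at about 74 homes, six fewer than 80 (6/80 = 7.5%).

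**If the 10% is spread evenly over two years (assumption).** Yearly retention is √0.90 = 0.9487. From 88, 83.5 reach randomisation. If all are randomised, 83.5 × 0.9487 = 79.2 finish. If only 80 are, 80 × 0.9487 = 75.9 finish, with power still about 0.81.

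**The case against.** The strongest reply is that nothing here changes a design decision. The formula error moves the recruitment target by one household, from 88 to 89, and the text says approximately 88. The 79.2 homes left still exceed the calculated 76. The four totals that miss by a household or more all belong to PFT or mold at f = 0.10 or 0.15 and are above 80 anyway. For f = 0.10 the article openly accepts that larger samples would be needed. All of this stands, and it sets the size of the point. It does not make the printed totals correct.

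A reader might also infer that randomisation is capped at 80, or that the reserve of eight homes is spent before randomisation. The document says neither. The 40 + 40 may be nominal figures for the target, the abstract says more than 80 households, and the intention-to-treat analysis takes in all randomised households. The 160 sensors would fit 80 homes at two each, but that allocation is itself an assumption. What remains is that the sections do not agree on a number and should.

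A reader might go further and conclude that power falls below 0.80. The stated 10% loss does not produce this: even with a cap of 80 and even attrition, power is about 0.81. Falling from 88 to 80 and then to 72 is a loss of 16 of 88, or 18%, not 10%. Homes that leave after randomisation also still contribute data under the planned mixed models and multiple imputation, so counts of completers overstate what is lost. At f = 0.15 or above, ACT and IAQ need 36 homes or fewer.

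The absence of separate loss allowances before and after randomisation is detail that an article may leave to the full protocol, and I do not count it as an error.

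**Conclusion.** Two minor corrections are warranted. The dropout adjustment in Table 1 uses the wrong formula: 15 of 21 adjusted totals are too small for a 10% loss, mostly by less than one household, and 88 recruited gives about 79 completers, not 80. This is plain arithmetic and rests on no assumption. Separately, recruiting 88 so that 80 is maintained throughout does not fit a device description for 80 homes after up to a year of possible losses. If 80 is read as the number randomised, every later loss goes below 80, though four homes of slack remain against the calculated requirement of 76. The power figures rest on correlation 0.5 and epsilon 1, which reproduce Table 1 closely but are not stated, and they concern only the smallest effect considered. No loss of power is demonstrated.

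**What to change.** 1. In Table 1, replace the adjusted row by N/0.90, rounded up. The f = 0.10 totals become 85 (ACT and IAQ), 223 (PFT) and 312 (mold), and the other twelve change as in the table above. Carry these into the Power calculations text: 84 becomes 85, 220 and 308 become 223 and 312, 53 becomes 54, and 26 becomes 27.
2. Either set the recruitment target at 89 to keep 80, or leave it at 88 and state that this gives about 79 completers after a 10% loss.
3. In Interventions, replace the fixed counts by a statement that all households completing the pre-intervention period are randomised, about 40 per device type (up to 44, which is 88/2). This agrees with Participant recruitment and Power calculations and lets the reserve cover losses after randomisation.

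Item 1 is an edit to the table and text. Item 2 costs at most one further household. Item 3 costs up to about 8 more devices in homes already enrolled, and further sensors if the 160 are sized for 80 homes. The article states that recruitment is ongoing and data collection has not begun, so all three can be settled before any home is randomised.

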### Interventions

The AIRVAC study will involve ERV and HEPA air cleaner interventions aimed at improving IAQ and asthma-related health outcomes. Following the pre-intervention period, participants will be randomized to receive one of four interventions during the 1-year post-intervention period: (1) active ERV, (2) sham (placebo) ERV, (3) active portable HEPA air cleaner, or (4) sham (placebo) portable HEPA air cleaner.

Due to the specific housing conditions required for ERV installation, including accessible ductwork for supply and exhaust, adequate space and access for the ERV unit, electrical safety, and proper sealing of penetrations, a constrained randomization approach will be employed. Prior to randomization, each home will undergo an ERV installation feasibility assessment based on the information collected during the initial walk-through visit (V0). Homes that meet the ERV installation criteria will be eligible for assignment to ERV or portable air cleaner study arms, whereas homes that do not meet the ERV installation criteria will only be eligible for portable air cleaner study arms.

After intervention eligibility is determined, participants will be randomly assigned to the available active or sham groups using a computer-generated randomization sequence in Stata (v.19) [35]. Stratified randomization will be used to maintain balance across the four study arms within predefined strata based on key housing and participant characteristics. Housing characteristics will include building envelope air leakage measured by blower door testing, home size, and exhaust fans, while participant characteristics will include baseline health status. The randomization sequence will be generated and securely maintained by the PIs. Allocation assignments will remain concealed until completion of eligibility confirmation and baseline assessments. All participants will remain blinded to whether they receive the active or sham intervention throughout the entire study duration. To maintain participant blinding, all field research staff and HVAC contractors will be trained not to disclose intervention assignments to participants.

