### Environmental exposure assessments

The study will involve the measurements of indoor criteria air pollutants, mold, and environmental conditions, including temperature and relative humidity (T/RH) to assess the magnitude of exposures in homes. Research-grade air quality sensors will be deployed for approximately one week during the four scheduled visits (V1–V4). The TSI Q-Trak XP IAQ monitor (7585) and DustTrak aerosol monitor (8530) will be placed alongside the indoor low-cost sensors to provide accurate measurements of size-resolved PM, NO_2_, NO, CO, O_3_, and formaldehyde (HCHO).

Additionally, low-cost sensors will continuously collect indoor and outdoor air quality data over the two-year study period. A total of 160 sensors will be fabricated using a microcontroller (Raspberry Pi 4 Model B, 4 GB) and multiple pollutant sensors, including a Sensirion SPS30 for PM, an Adafruit SGP30 for VOCs, an Amphenol MiCS-2714 for NO_2_, and a Sensirion SCD4x for CO_2_ and T/RH, with an estimated cost of approximately $150 per unit. Those economically viable sensor selections are verified in a similar study to measure indoor environmental quality for residential buildings [37]. The low-cost air quality sensors will be deployed indoors (primarily in the living room) and outdoors (primarily in the backyard or porch area) during the first follow-up visit (V1) and will remain in place throughout the study. For each visit, the research team will log the senor readings to check the quality of data collection with proper tech maintenance on the sensors. Long-term time-series data from these sensors will be calibrated against short-term (approximately 1-week) high-accuracy measurements measured by research-grade instruments, and additional details on the calibration process are provided in the Statistical Analysis Plan section.

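### The relocation exclusion covers only planned moves out of the DFW area, so a household already planning a move within DFW passes screening although the design is bound to the enrolled house (minor)

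*Protocol article*

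**What the plan says.** Three eligibility statements in the Protocol article, Participant recruitment, bear on where a household lives during the trial, besides the relocation exclusion itself.

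- The exclusion is limited to an anticipated "relocation outside the DFW area within the two-year study period".
- The residency criterion is set at the same geographic level: "Residency in the DFW area".
- The tenure requirement is that "homes must be owner-occupied".
- The commitment requirement is that "participants must agree to participate in the entire 2-year study duration and allow for five home visits by the research team".

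The design sections fix the trial to the house. Under Interventions, eligibility for the ERV arms is decided from the V0 walk-through of each home, and for stratification "Housing characteristics will include building envelope air leakage measured by blower door testing, home size, and exhaust fans". Also there: "The ERV units will then operate continuously at the specified ventilation rate throughout the intervention period". Under Environmental exposure assessments, the indoor and outdoor low-cost sensors are put out at V1 and "will remain in place throughout the study". Mold is sampled in each home at V1 and V4. The statistical analysis section applies intention-to-treat to all randomised households.

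**The concern.** The plan already treats a foreseeable move as a reason not to enrol. The boundary it uses is the metropolitan area, while what is randomised, fitted out and measured is a house. A move across town takes a family away from an installed ERV, the sensors and the house baseline, just as a move out of the area does, but only the second is screened out.

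At stake are the pre/post comparison of air quality and mold in all four arms, and the duration of exposure in the two ERV arms. Intention-to-treat keeps such a household in its arm, as it should. Lost ERV exposure would therefore pull the active-versus-sham ERV contrast towards zero. A portable air cleaner can go with its owner and a ducted ERV cannot, so the same move could also bear unequally on the planned comparison of active ERV with active air cleaner.

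**Working it through.** The point concerns the scope of a criterion and the plan states no related figure, so there is nothing to recompute. Two questions need a reading of the text.

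**1. Does any other criterion stop a household that plans a move within DFW?**

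- Residency: no. The household is a DFW resident before and after the move.
- Owner-occupation: no. It is met at screening, and nothing listed requires it to continue at the same address.
- Two years and five home visits: not explicitly. The clause does not name the enrolled home, so a household could agree in good faith and expect later visits at a new address.
- The remaining items (diagnosis, age, language, consent, phone contact, smoking, hazards, other devices) do not touch the question.

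As written, such a household passes.

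**2. What would a move within DFW break?**

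| Element | Protocol section | Tied to | After the move |
|---|---|---|---|
| Blower-door leakage and housing survey | Study design | House | Describes the former house |
| ERV feasibility, which decides the arms open to the home | Interventions | House | Describes the former house |
| Strata: leakage, home size, exhaust fans | Interventions | House | Describe the former house |
| Stratum: baseline health status | Interventions | Participant | Carries over |
| Active or sham ERV; airflow set from floor area, bedrooms and leakage | Interventions | House | Exposure ends |
| Active or sham air cleaner | Interventions | Portable unit placed in a room | Could move with the family |
| Indoor and outdoor low-cost sensors | Environmental exposure assessments | House | Series broken |
| Mold samples at V1 and V4 | Environmental exposure assessments | House | The pair may span two houses |
| Monthly ACT by online link | Health outcome assessments | Participant | Continues |
| ACQ and spirometry at V1–V4 | Health outcome assessments | Participant, during a home visit | Can continue within DFW |

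Timing matters too. The pre-intervention period lasts up to one year. A move before randomisation makes the V0 feasibility and housing strata out of date; a move afterwards ends ERV exposure and splits the before and after measurements between two houses.

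**3. What numbers bound it?** The documents plan 40 ERV homes and 40 air cleaner homes, so loss of the device itself is certain only for movers among 40 of 80 homes. The recruitment margin is 88 − 80 = 8 households for all causes of dropout. No rate of planned moves within DFW is given, so no count of affected homes and no dilution of effect can be derived.

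**The case against.** The strongest reply is that the gap is narrow. The criterion screens only for moves a household already expects and would report. Homes are owner-occupied, recruitment is mainly from applicants to a home-repair and accessibility program, and participants agree to two years and five visits. People seeking repairs to a house they own are not likely to be planning to leave it. This stands, and it limits the severity.

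A second reply is that limiting the exclusion to moves out of DFW has a rationale: within DFW the participant stays reachable and the asthma outcomes can still be measured. That also stands for ACT, ACQ and spirometry. It does not answer the loss of ERV exposure or of continuity in the air quality and mold data, which belong to the primary objective.

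A third is that plug load loggers and the per-protocol analysis would deal with movers. This helps only in part. A logger shows whether a unit is running, not who lives in the house, and a per-protocol set cannot restore a broken sensor or mold series.

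Finally, the screening form and the full protocol are not shown. The form may already ask the right question, and a rule for mid-study moves may exist. The absence of such a rule is not counted here. The point rests on the stated criterion, which as worded admits foreseeable movers.

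A reader might go further and infer that every mover loses the assigned device, or assume a move rate and set the resulting number of homes against the margin of 8 while also computing a dilution of the treatment effect. The documents support neither. Air cleaners are portable; any rate would be unanchored; for a given outcome a home is either missing or diluting, not both; and moves before randomisation need not enter the post-intervention contrast at all.

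**Conclusion.** The concern holds as a mismatch between the geographic unit of one exclusion criterion and the house-based design. In the ERV arms a planned move within DFW would end exposure. In every arm it would break the continuity of the sensors, the mold samples and the house-based feasibility and stratification data. The questionnaire and spirometry outcomes need not be lost.

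Its size cannot be calculated from the documents and is probably small, on the assumption that owner-occupation, the recruitment source and the two-year commitment make planned moves uncommon. Unforeseen moves are a separate matter that the dropout allowance exists to absorb, and no screening rule would prevent them. Severity: minor.

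**What to change.** Reword the exclusion to: *anticipated relocation from the enrolled home during the two-year study, whether inside or outside the DFW area*. Check that the relocation question on the electronic screening form matches, and change it only if it does not. Put the question again to households already screened but not yet randomised; at the time of writing recruitment was under way and data collection had not begun, so this can still be done early.

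The cost is one phrase in the criteria, possibly one on the form, a brief re-check of households already screened, and the exclusion of a few more. No change to the sample size or the analysis is needed.
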